### Proximal massage

2.7

1.Spine pinching: will be performed from the tip of coccyx on the midline of the back to the spinous process of the seventh cervical vertebra, through pinching and lifting 3 times along the spine (× 7 repetitions);2.abdomen kneading: will be performed by massaging the abdomen clockwise with the palms (× 100 repetitions).

#### Control group

2.7.1

Jianweixiaoshi tablets (national medicine approval Z36021464) will be administered as follows:

(1)aged 2 to 6 years: 2 tablets/time;(2)aged 7 to 12 years: 3 tablets/time with chewing 3 times/d.

#### Blank group

2.7.2

No interventions will be performed.

### Randomized grouping

2.8

A total of 60 healthy children will be randomly selected for physical examinations. A statistical expert not involved in the design of the study will use SPSS 22.0 software to generate a series of random sequences, which will be marked onto a card and placed in a sealed envelope. Each subject will receive an envelope at a time-point consistent with the test conditions. Subjects will be randomly divided based on their number into control or test groups (n = 60 per group). For each child, the chiropractor will open the envelope to obtain the grouping code.

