**Methods::**

A total of 60 healthy children will be randomly selected for physical examination. According to a random number generated by a computer, children with anorexia who meet the inclusion criteria will be selected. In strict accordance with the time sequence of inclusion, subjects will be randomly assigned to either the massage or control group (n = 60 per group). The blank group will receive no treatment. Children in the massage group will receive a designated massage protocol. The control group will be administered oral Jianweixiaoshi tablets over 4 weeks. Each group will be compared for intestinal flora structure, fecal short chain fatty acids levels, serum trace elements, urine D-xylose-excretion rates, gastric fluid emptying, gastric motility, and hemoglobin levels before and after treatment.

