### Limb Massage

2.6

1.Massage will be performed using the thumb radial finger to the finger root (× 200 repetitions).2.The palm and tip of the thumb will be used to rub the horizontal grain of the proximal interphalangeal joint of the index finger, middle finger, ring finger, and little finger (× 100 repetitions).3.Kneading of the thenar will be performed with the thumb-end (× 100 repetitions).4.The PC8 (located in the center of the horizontal grain of the palm, in the middle of the second and third metacarpal bones) will be used as the center of the circle and rubbed clockwise with the thumb abdominal (× 100 repetitions).5.The ST 36 (located at the lower margin of the patella) will be pressed to 3 inches in the depression of the lateral patellar ligament by transversing the finger next to the anterior tibial ridge with low levels of force using the thumb or a threaded surface (× 150 repetitions).

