#### Statistical analysis

2.11.6

SPSS22.0 statistical software will be used for all analysis. Data will be graded using rank sum tests. *χ*^2^ tests will be used for data counts. Measurement data will be shown as the mean ± standard deviation. Data with a normal distribution will be analyzed using a 1-way analysis of variance. Least Significant Difference tests will be adopted for parity of variance. A Games–Howell test will be adopted for data with a non-normal distribution. The rank sum test was used for those who did not conform to normal distribution. *P* < .05 will be considered statistically significant.

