## Discussion

3

The intestinal flora forms a large and complex micro ecosystem that plays an important role in the maintenance of human health, including the normal function of the gastrointestinal tract.^[10]^ During childhood, disturbances in the intestinal flora can occur due to the relatively immature micro ecological environment,^[11]^ leading to effects on the neuroendocrine system that lead to a loss of appetite and food intake,^[12]^ increasing the risk of anorexia. The main metabolite of intestinal flora are SCFAs.^[13]^ SCFAs specifically bind to G-protein-coupled receptors in the intestinal tract^[14]^ to activate endocrine cells to secrete appetite-suppressing hormones, leading to a loss of appetite.^[15]^ Approximately 5% of SCFAs are excreted in the feces^[16]^ providing a relatively reliable and stable detection index for anorexia.

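### Age band sets the tablet regimen but appears in neither the described allocation nor the stated tests, so a chance age imbalance would go uncorrected (minor)

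*Protocol article*

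**What the plan says.** Section 2.3 of the protocol article (Inclusion criteria) admits ages 2 to 12. Section 2.7.1 (Control group) splits that range: "1)aged 2 to 6 years: 2 tablets/time;(2)aged 7 to 12 years: 3 tablets/time with chewing 3 times/d". The massage is not split. Sections 2.6 and 2.7 give one set of counts for every child, for example "Massage will be performed using the thumb radial finger to the finger root (× 200 repetitions" and "abdomen kneading: will be performed by massaging the abdomen clockwise with the palms (× 100 repetitions".

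On allocation, section 2.8 (Randomized grouping) says "Subjects will be randomly divided based on their number into control or test groups (n = 60 per group", and the abstract says "In strict accordance with the time sequence of inclusion, subjects will be randomly assigned to either the massage or control group (n = 60 per group". Section 2.8 speaks of random sequences in the plural, kept in sealed envelopes. It does not say whether they are stratified.

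On analysis, section 2.11.6 says "Data with a normal distribution will be analyzed using a 1-way analysis of variance", with a rank sum test where normality fails and a P value threshold of "< .05 will be considered statistically significant". No covariate is named.

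Two further statements bear on age. The Discussion says "During childhood, disturbances in the intestinal flora can occur due to the relatively immature micro ecological environment", and the Introduction places the disease mostly at 1 to 5 years.

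**The concern.** Age band is the one patient characteristic that the protocol itself uses to divide the comparator regimen. The main outcomes, intestinal flora and faecal short chain fatty acids, may well differ between a 3-year-old and a 10-year-old. The Discussion's remark on immature flora points that way, although it gives no gradient within the 2 to 12 range.

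The band is known for every child before the envelope is opened, so it could be balanced or adjusted for at almost no cost. As described, the plan does neither. If one arm happened to receive more older children, the unadjusted arm difference would carry part of the age difference, and nothing in the stated tests would remove it. Some precision would also be lost, because variation between bands stays in the error term.

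**Working it through.** The article gives no sample-size calculation, so there is no figure of its own to reproduce.

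**Inputs from the document.** 60 children per randomised arm, 120 in all; ages 2 to 12; 2 against 3 tablets per time; significance level 0.05 (sidedness not stated, taken as two-sided).

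**Assumed inputs.** Share *p* of randomised children aged 7 to 12: 10% to 50%. Outcome difference *e* between bands: 0.2 to 0.8 within-band SD. The document gives neither.

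**1. Regimen step.** 3/2 = 1.5 per administration in the tablet arm; no step in the massage arm.

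**2. Chance imbalance.** With K = 120*p* older children, the number X in one arm is hypergeometric. The gap in share is |2X − K|/60, and the SD of the signed difference is √(4*p*(1 − *p*)/119). For *p* = 0.3 this is √(0.84/119) = 0.084.

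| Older share | SD (points) | Smallest gap covering at least 95% of allocations (points) | P(gap ≥ 10 points) | P(gap ≥ 15 points) |
|---|---|---|---|---|
| 10% | 5.5 | 10.0 | 12.5% | 0.4% |
| 20% | 7.3 | 13.3 | 25% | 4% |
| 30% | 8.4 | 16.7 | 32% | 7% |
| 40% | 9.0 | 16.7 | 35% | 9% |
| 50% | 9.2 | 16.7 | 36% | 10% |

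**3. Shift in the unadjusted arm difference.** Shift = gap × *e*. At the 95% gaps of 0.100 to 0.167:
- *e* = 0.2: 0.02 to 0.03 SD
- *e* = 0.5: 0.05 to 0.08 SD
- *e* = 0.8: 0.08 to 0.13 SD

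The standard error of the arm difference is √(2/60) = 0.183 SD, so the largest shift is 0.133/0.183 = 0.73 standard errors.

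**4. Type I error given a gap of that size.** This is P(|Z + shift/0.183| > 1.96 × √(1 + *p*(1 − *p*)*e*²)). For *p* = 0.3 and *e* = 0.8 the threshold is 1.96 × √1.1344 = 2.09, and the result is 9.0%. Over the range of *p* the results are 5.1% to 5.3% for *e* = 0.2, 5.6% to 6.7% for *e* = 0.5, and 6.4% to 9.0% for *e* = 0.8.

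**5. Type I error over all allocations.** With 20,000 simulated re-randomisations in each of four scenarios (*p* = 0.2 or 0.4, *e* = 0.5 or 0.8) and an unadjusted t-test, the rate was 4.9% to 5.1% and the mean shift was within 0.004 SD of zero.

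**6. Power for a 0.5 SD effect.** With band in the model: Φ(0.5/0.183 − 1.96) = Φ(0.78) = 78%. Without it, the SD rises to √(1 + *p*(1 − *p*)*e*²). That is 1.020 at *p* = 0.2, *e* = 0.5 (power 77%) and 1.074 at *p* = 0.4, *e* = 0.8 (power 72%).

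**The case against.** The strongest reply is that nothing here is wrong. Randomisation without strata is valid, and step 5 confirms that chance imbalance is already covered by the 5% error rate. A condensed article commonly leaves strata, blocks and covariates to a fuller document, and allocating in order of inclusion is compatible with strata. The age effect is assumed, not documented. Outcomes are measured before and after treatment, so an analysis of change would cancel much of any stable age difference in level. The Introduction points to a mostly younger sample, where imbalance is smaller.

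Most of this stands, and it is why the point is minor. It does not remove the point, because section 2.11.6 is not merely silent: it names a one-way analysis, which by construction has group as its only factor.

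Three stronger readings are tempting, and the document supports none of them.

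- *Control dose is a second confounder.* Dose is fixed by age and exists only in the tablet arm. Age-banded dosing is part of the comparator regimen; only age can be imbalanced between arms.
- *The protocol specifies a single unstratified sequence.* Section 2.8 says neither; it names no strata.
- *Balancing would remove a difference in effect between bands.* It equalises the age mix, but the pooled result would still average two contrasts. Reading the bands separately is possible without stratification and is weak either way. If 30% of children are older there are 18 per arm, and power for a 0.5 SD effect is about Φ(0.5/√(2/18) − 1.96) = Φ(−0.46) = 32%.

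**Conclusion.** The point holds as a cheap improvement. A reader might infer that the massage-versus-tablet comparison is biased or its error rate inflated; it is not, because the shift averages to about zero over allocations. What remains is that the one allocation actually drawn may be unbalanced by age band, with no stated means of correcting for it. The plausible cost is small: a shift of at most about 0.13 SD at the 95% imbalance, and 1 to 6 percentage points of power for a 0.5 SD effect (72% to 77% against 78%).

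These sizes rest on an assumed older share and an assumed band effect, on continuous outcomes compared without baseline adjustment, and on a two-sided 5% test. With few older children or a band effect near 0.2 SD, the shift is negligible. Severity: minor.

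**What to change.** 1. **Analysis.** For the massage-versus-control comparison, replace the one-way analysis of variance with a linear model containing arm and age band (or age). Where a rank test is needed, use one stratified by band. State this before the data are unblinded. It costs one degree of freedom and can be done even if enrolment is complete.
2. **Allocation, for children not yet randomised.** Prepare separate computer-generated sequences and envelope sets for ages 2 to 6 and 7 to 12, with concealed block sizes that vary. If strata already exist in a fuller document, say so in section 2.8.

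The allocation change has two small costs. Arm totals may miss 60 by a few if the last blocks are incomplete. Blocks also make later assignments slightly more predictable, which matters because section 2.8 has the chiropractor, apparently the person who gives the massage, open the envelopes. Varying, concealed block sizes limit this without removing it. If it is judged unacceptable, the analysis change alone gives most of the benefit. Neither change touches any dose or treatment rule.

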### Single-Blinding

2.9

The massage doctor will have no prior knowledge of the grouping information or treatment regimen contained in the envelope. All participants and relevant health care personnel will not interfere with the study. The evaluator will not be aware of the treatment protocol received by each subject and instructed family members will be asked to complete all relevant study scales. Statisticians will be blinded during all statistical analysis.

### End of study/discontinuation

2.10

The study will be discontinued when the following complications are encountered:

(1)serious adverse events or specific physiological changes;(2)voluntarily discontinuation;(3)poor compliance, including a failure to cooperate or comply with treatment after repeated explanations by the clinician;(4)receiving food or alternative treatments for anorexia;(5)results of those exceeding half of the total course of treatment available for inclusion in the statistical analysis of treatments.

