## Introduction

1

Feeding disorders fall into 3 categories under the Chatoor criteria:^[1]^

(1)feeding disorders of state regulation;(2)feeding disorders of reciprocity; and(3)pediatric anorexia (PN).

PN refers to children with a sustained loss of appetite, who eat less and/or dislike eating. As a disorder of chronic hunger, PN is common in children, with a prevalence of 5% to 10%.^[2]^ The disease is most common in children aged 1 to 5 years.^[3]^ If left untreated, PN can result in childhood malnutrition, body wasting, rickets, anemia, and a decline in immune function, all adverse consequences that can affect growth and development both physically and intellectually, in addition to mental illness.^[4–5]^ In modern medicine, the main treatment for PN is drug treatment, including the use of supplementary trace elements to enhance peptin levels and gastric dynamics^[6]^ However, it is often difficult to determine the exact cause of anorexia in children.^[7]^ Due to the poor compliance of children on oral drugs and the high occurrence of side effects,^[8]^ their clinical application is limited.

As a painless and non-drug therapy, infantile massage is widely applicable to the pediatric disease spectrum, with the advantages of simple operation and a comfortable experience. In clinical practice, massage represents a dominant therapy for PN. Through many years of clinical practice, it has been shown that children with anorexia who receive massage therapy not only significantly improve their appetite, but relieve sallow complexion, abdominal distension, and other accompanying symptoms. Modern medical studies have shown that massage therapy can increase vagus nerve activity and promote appetite regulatory factors, thus increasing gastrointestinal peristalsis^[9]^ and improving digestive function. Massage intervention also correlates with improves the correlation between the brain and intestine axis, intestinal flora activity, and the regulation of host metabolism.

In this study, we explore the biological mechanism(s) of anorexia from the perspective of intestinal flora and the regulation of host metabolism. We further reveal the action site and therapeutic mechanism(s) of pediatric massage for the treatment of anorexia. This furthers our understanding of the optimal treatment methods for the treatment of PN in the clinic.

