### Inclusion criteria

2.3

All subjects will be required to meet the known diagnostic criteria for anorexia in children.^[1]^ The criteria include

(1)a refusal to eat adequate amounts of food for at least 1 month;(2)a failure to communicate hunger and a lack of interest in food;(3)significant growth deficiency;(4)a refusal to eat that is unrelated to an underlying medical illness or a traumatic event;(5)aged 2 to 12;(6)agree to receive massage therapy;(7)consent to the study either directly or through a legal guardian.

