Massaging is a medical method to prevent and cure diseases of specific limb movements in the human body. Massaging is non-invasive, easy to obtain cooperation, and shows high safety. It also shows good application prospects for alternative drug therapy in children with anorexia, and has been shown to be effective for alleviating functional digestive associated diseases.^[17–19]^ The traditional Chinese massage theory suggests that both distal treatment of the meridian of the limbs and proximal treatment (local treatment such as kneading the spine and abdomen) can restore gastrointestinal function. The effects of distal treatment result from its influence on the autonomic nervous system and childhood psychology. By massaging the limbs, the peripheral blood flow is increased, the autonomic nervous system is activated, and the gastrointestinal parasympathetic nerve is excited.^[20]^ During massage, comfortable physical contact can also relieve anxiety and shorten the psychological distance between massage doctors and children.^[21]^ The mechanism of proximal treatment is mainly physical, by stimulating local acupoints and their meridional locations, the mechanical power of manipulation can be used to directly affect gastrointestinal muscle groups, thereby stimulating intestinal smooth muscle, promoting peristaltic function, reducing gastric residual volume and improving digestion.^[22]^ Continuous stimulation through massage can transform mechanical energy into heat energy, promoting intestinal blood circulation and alleviating gastrointestinal dynamic abnormalities. However, a lack of relevant research on the regulatory mechanisms of intestinal flora by massage therapy exist. In this study, we will provide new evidence for the regulation of intestinal flora in response to massage.

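### The half-course rule in section 2.10, on its natural reading, lets exposure after randomisation decide which children who stop treatment are analysed

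*Protocol article*

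**What the plan says.** Section 2.10 (End of study/discontinuation) gives five numbered items. The first four are reasons for stopping: serious adverse events or specific physiological changes, voluntary withdrawal, "poor compliance, including a failure to cooperate or comply with treatment after repeated explanations by the clinician", and "receiving food or alternative treatments for anorexia". The fifth is not a reason for stopping but a statement about the analysis: "results of those exceeding half of the total course of treatment available for inclusion in the statistical analysis of treatments".

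Section 2.11.6 (Statistical analysis) names tests but no analysis population. Nowhere does the article say that all randomised children are analysed in their assigned group.

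Two other places bear on how the arms may differ. The Introduction says that the clinical use of drug treatment is limited, "Due to the poor compliance of children on oral drugs and the high occurrence of side effects". The Discussion says of massage: "Massaging is non-invasive, easy to obtain cooperation, and shows high safety", and section 4 (Advantages) adds that children accept it readily. The comparator is an oral tablet: "The control group will be administered oral Jianweixiaoshi tablets over 4 weeks".

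**The concern.** A threshold of more than half the course has a purpose only if children below it are treated differently. Read that way, item (5) removes from the analysis children who stop early for any of the four listed reasons. All four arise after randomisation and may be related both to the assigned treatment and to the outcome. The children left in each arm are then no longer the groups that randomisation created.

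The harm comes from unequal exclusion, or from different kinds of children being excluded in the two arms. The article's own contrast between oral drugs and massage gives reason to expect that. Allocation is also known where compliance is judged. The practitioner opens the envelope (section 2.8), the clinician who repeats the explanations deals with a family that knows whether the child gets massage or tablets, and blinding the statistician does not undo a selection made earlier. At stake is the massage-tablet comparison on the main and secondary outcomes.

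**Working it through.** **Nothing to reproduce.** The article gives 60 children per group and a 0.05 significance level, but no effect size, SD, power or expected loss. What follows is an illustration.

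**Inputs from the article**
- 60 massage and 60 control children (section 2.8).
- Significance level 0.05 (section 2.11.6); two-sided is assumed.
- Tablets for 4 weeks (Abstract), so halfway is 2 weeks in that arm.

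**Assumed inputs**
- Excluded share in massage, fm = 5%; in control, fc = 10%, 20% or 30%.
- Gap s between the mean of retained and of excluded children in the same arm: 0.5 to 1.0 SD, the same in both arms.
- Total SD 1 and no true treatment effect.

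**Step 1: bias.** If the retained mean is R and the excluded mean is R − s, the mean of the whole arm is (1 − f)·R + f·(R − s) = R − f·s. The retained mean therefore exceeds the whole-arm mean by f·s, and the between-arm difference is shifted by

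bias = (fc − fm)·s.

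**Step 2: type I error.** The variance within the retained children is taken as 1 − f(1 − f)s², with 60(1 − f) children per arm, in a two-sided z-test at 0.05.

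| Excluded, massage / control | Analysed | Bias, s = 0.5 | Bias, s = 1.0 | Type I error |
|---|---|---|---|---|
| 5% / 10% | 57 / 54 | 0.05 × 0.5 = 0.025 | 0.05 × 1.0 = 0.05 | 0.052 to 0.059 |
| 5% / 20% | 57 / 48 | 0.15 × 0.5 = 0.075 | 0.15 × 1.0 = 0.15 | 0.067 to 0.128 |
| 5% / 30% | 57 / 42 | 0.25 × 0.5 = 0.125 | 0.25 × 1.0 = 0.25 | 0.096 to 0.264 |
| 20% / 20% | 48 / 48 | 0 | 0 | 0.05 |

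**Step 3: yardstick.** With 60 per arm, two-sided 5% and 80% power, the detectable difference is 0.516 SD from the t-test. The normal approximation, (1.960 + 0.842) × √(2/60), gives 0.511. For the 20% and 30% rows the smallest and largest biases are 0.075/0.516 = 15% and 0.25/0.516 = 48% of it.

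**Step 4: sign.** If early stoppers do worse (s > 0), dropping more of them from the tablet arm flatters tablets. If they stop because they have improved (s < 0), it flatters massage. The article does not say which applies.

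The scale suits continuous outcomes such as a short chain fatty acid level. Flora structure has no single SD scale, so the figures do not carry over to it directly.

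**The case against.** The strongest reply is that item (5) never says that other children are left out. It says that certain results may be included, and it could be a permissive note that data from late stoppers are kept. That is a possible reading of garbled text, so the exclusion is an inference. It remains the natural one, since a threshold that excludes nobody would serve no purpose. A separate analysis plan might define other populations, but it would have to override a rule that the article states.

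Four stronger readings are tempting, and the documents do not support them:

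- *All poor compliers are excluded.* Section 2.10 discontinues them, but one who stops after halfway is still analysed.
- *The rule demonstrably strips the tablet arm.* The Introduction speaks of oral drugs in general, not of this tablet, and section 5 (Limitations) describes the control drug as long used with proven safety and efficacy. Unequal loss is plausible, no more.
- *Inclusion criterion 6, "agree to receive massage therapy", drives families allocated to tablets out of the trial.* Criterion 7 also requires consent to the study, and section 2.2 has the full study content explained and consent signed. The chain from this criterion to exclusion is speculation.
- *The bias is larger.* Measuring the deficit against the whole-arm mean gives f·s/(1 − f) per arm, and so 0.10 to 0.38 SD over the 20% and 30% scenarios. That amounts to assuming a wider gap between excluded and retained children; in the ordinary sense of the gap, the table above applies.

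It is also fair to say that the bias is not wholly hidden. Outcomes are measured before treatment, so exclusions by arm and their baseline values can be reported. That would describe the selection without removing its effect.

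**Conclusion.** The point holds in a limited form. On its natural reading, item (5) is a stated analysis rule based on exposure after randomisation, not a detail left to another document, and nothing in the article commits to analysing all randomised children as assigned. The rule can bias the massage-tablet comparison. Whether it will, by how much and in which direction cannot be settled from the documents.

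Under the assumed 20% or 30% exclusion on tablets against 5% on massage, with a gap of 0.5 to 1.0 SD, the bias is 0.075 to 0.25 SD. At 10% against 5% it is at most 0.05 SD, and with equal exclusion and equal gaps it is zero. Confidence is moderate, because the exclusion is inferred from unclear wording and every rate is assumed. The correction is worth making early all the same: a stool sample not collected from a child who stops cannot be recovered later.

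**What to change.** Take item (5) out of the discontinuation list, where it does not belong, and leave the clinical reasons for stopping as they are. Put in its place: *All randomised children are analysed in the arm to which they were randomised. Planned end-of-treatment measurements are sought at the planned time whether or not study treatment was stopped, unless consent is withdrawn.*

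Add a pre-specified missing-data method for children without end measurements. Keep the more-than-half-course set as a labelled per-protocol sensitivity analysis, and report exclusions from it by arm with reasons.

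The cost is a wording amendment, some extra effort to obtain end samples from children who stop, and possible dilution of the estimate by non-adherence. With complete outcomes on all 60 + 60 children, the bias from exclusion is zero. With incomplete follow-up, what remains depends on the missing-data method.
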